### Randomization and allocation concealment

Block randomization will be applied in this study. The participants will be divided into the “coma group”, “MCS group” or “VS group”, depending on their type of consciousness disorder. Each eligible participant will then be randomly assigned to either the intervention group or control group according to the 1:1 equal proportion rule. The sequence of random allocation will be generated using the PLAN function of the statistical software SPSS 24.0 (IBM,USA); this will be undertaken by an independent statistician from the Center of Evidence Based Medicine, NCU, who will not be involved in this trial. Also, the sequence of random allocation will be concealed to outcome assessors and the statistical analyst. The eligible participants’ allocation will also be concealed from their caregivers and from the therapists (including acupuncturist and cognitive therapists) after the participants’ baseline information has been assessed, and the therapists will be arrange the patients’ allocated treatments.

### Blinding

Due to the double-blind implementation of this study, “third party” personnel who are not involved in the experiment will manage and supervise the implementation of the blinding method: (1) the computer-generated random numbers are placed in an airtight envelope. The patients receive the envelope according to the order of their inclusion in the study and are not allowed to open the envelope. The tDCS stimulator mode has been preset as A mode and B mode, and the specific implementer of the project does not know what kind of stimulation AB represents (A is active stimulus, B is sham stimulus); (2) according to the principle of the blinding method, the efficacy of the treatment is evaluated by the third-party evaluators who do not know the grouping. The evaluators do not participate in the recruitment and treatment of patients, and the researchers, operators and statisticians work separately and independently; (3) in order to prevent the subjective tendency of the analyst in the process of data analysis, the first unblinding is performed before the completion of the statistical analysis, that is, the analyst knows that the patients are divided into two groups, but does not know which is the intervention group. After the statistical analysis, the second unblinding is performed to determine which group is the intervention group.

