### Trial status

This protocol version number is V2.1(2019082201). Participant enrollment will start in December 2019. The trial is expected to be completed by the end of December 2020.

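### The published protocol prints the key to the stimulator modes (A active, B sham) before enrolment starts, so the operator blinding it claims does not hold as written

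*Protocol article*

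**What the plan says.** The Blinding section puts third-party staff in charge of the blind. On the device it states: "The tDCS stimulator mode has been preset as A mode and B mode". It goes on to say that "the specific implementer of the project does not know what kind of stimulation AB represents (A is active stimulus, B is sham stimulus".

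For the analysis there are two steps. At the first, "the analyst knows that the patients are divided into two groups, but does not know which is the intervention group". Then: "After the statistical analysis, the second unblinding is performed to determine which group is the intervention group".

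The section on randomization and allocation concealment says that "the sequence of random allocation will be concealed to outcome assessors and the statistical analyst", and that the participants' "allocation will also be concealed from their caregivers and from the therapists". The Blinding section adds that efficacy is judged by third-party evaluators who are unaware of the grouping and take no part in recruitment or treatment.

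On timing, the article carries the date 17 October 2019. Trial status says: "Participant enrollment will start in December 2019" and "The trial is expected to be completed by the end of December 2020".

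**The concern.** Blinding the operator by a mode letter works only while the meaning of the letter is secret. Here the meaning is printed in the published protocol, in the sentence that says the operator does not have it. Therapists and operators are natural readers of this article: the Intervention section says their procedures are to be standardized, with the study protocol named among the items covered.

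The Discussion presents the double-blind design as what secures the authenticity of the results. Operators treat each patient six times a week for 4 weeks. An operator who knows the arm could influence the comparison without ever rating an outcome:

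- **Concurrent care.** The limb electrical stimulation section gives no numeric intensity, and the hyperbaric oxygen section allows either of two breathing schedules. Both leave room for care to differ by arm.
- **Withdrawal.** Under Study endpoints, suspension for non-cooperation depends partly on the dealings of treatment staff with the patient. The Statistical analysis section fills missing data by last observation carried forward, so withdrawal that differs by arm would carry into the results.
- **Leakage.** The arm could be passed on to other staff or to the family. The data collection section allows contact with family members by telephone to complete an assessment.

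**Working it through.** The plan gives no figure on this point to reproduce. The check is a comparison of the text with itself, plus date arithmetic.

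**1. Is the claim contradicted by its own sentence?**

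- Claim: the person running the device does not know what A and B stand for.
- Same sentence, in parentheses: A is active, B is sham.
- The presets are described as already made, so this is a mapping in place. Nothing in the article says that it is illustrative or will be changed after publication.

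**2. When does the key become public relative to treatment?**

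Inputs: article date 17 October 2019; enrolment start December 2019 (day not given, so taken as 1 to 31 December); completion by the end of December 2020.

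- 17 October to 1 December 2019: 14 + 30 + 1 = 45 days; 45 / 7 = 6.4 weeks.
- 17 October to 31 December 2019: 14 + 30 + 31 = 75 days; 75 / 7 = 10.7 weeks.
- 17 October 2019 to 31 December 2020: 75 + 366 = 441 days (2020 is a leap year).

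The key is public about 6 to 11 weeks before the first patient and for the whole planned trial.

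**3. Who is exposed?**

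| Role | What the article says | Effect of the printed key |
|---|---|---|
| Operator or therapist | Device runs in mode A or B; meaning said to be unknown to the implementer | Direct: letter plus article gives the arm |
| Analyst | Sees two groups, identity withheld until the second unblinding; sequence concealed | Conditional: fails only if the groups are labelled with the device letters, which is not stated |
| Outcome evaluators | Separate from recruitment and treatment; do not know the grouping | No direct effect; would need leakage |
| Patients | Have disorders of consciousness; sham uses the same electrode placement | Not defeated by the key itself |

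The operator row assumes that whoever sets the device sees the letter. The article does not say so outright, but its statement that the implementer does not know what the letters mean is needed only if the letters are seen.

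**4. Is the analyst row a real risk?** A and B are the only treatment codes named, and no relabelling for the analysis file is described. Table 1 lists a therapeutic parameter record in each of the 4 treatment weeks, but does not say that it holds the mode letter or reaches the analyst. The risk is open, not shown.

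**The case against.** The strongest reply is that the printed key touches only one layer of the blind. The people who produce the primary outcome are not the operators. The Blinding section separates evaluators from treatment, the Outcome measures section requires independent blinded assessment, and the data collection section has data gathered by investigators blind to allocation. The Blinding section also has operators and statisticians work independently, and the sequence is concealed from the analyst. All of this stands, and it limits the consequence: the documents do not support a claim that the GOS ratings are unblinded.

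A reader might infer that the analyst is certain to be unblinded. The article does not say that the analysis file carries the device letters, so this remains conditional. A reader might also infer that all 80 allocations are readable. That would require someone to see the mode letter of every patient, and the article does not say who sees which letters.

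It is also fair to say that one pair of letters for all patients, with a secret key, is a weaker choice than patient-specific codes but not an error. Details of code format are commonly left to a fuller document. That part is a preference, and nothing shows that a stimulator with two presets can take individual codes.

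What the reply does not answer is the contradiction itself. Separate evaluators do not restore the operator blinding that the article expressly claims, and they do not remove the routes through concurrent care and withdrawal.

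**Conclusion.** The point holds for operator blinding. The article claims that operators do not know what the mode letters mean and publishes that meaning 45 to 75 days before enrolment could begin. As written, an operator or therapist who sees the letter and has read the article knows that patient's arm.

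This rests on two assumptions: that the person setting the device sees the letter, and that the printed mapping is the one used. Nothing in the article says otherwise on either.

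The size of any resulting bias cannot be computed from the document. The article does not show that anyone was unblinded. It shows that a stated safeguard fails on its own text. The effect on the GOS would be indirect, through leakage, differences in concurrent care or differential withdrawal. Failure of the analyst's blind depends on labels that the article does not specify. A reading that the whole double-blind design collapses goes further than the text allows.

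The correction still needs to come before the first patient, because an operator's knowledge of the arm during treatment cannot be undone afterwards.

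**What to change.** Before first enrolment:

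1. The independent third party secretly re-draws which preset is A and which is B, so that the printed mapping no longer tells a reader anything. Patient-specific codes would also serve if the device allows them; re-drawing the two presets is enough to cure the printed key.
2. The new key is held only by the third party and kept out of all protocol versions and publications until the second unblinding.
3. The analyst receives group labels drawn independently of the device letters, and the mode letter is left out of the analysis file.
4. The Blinding section is corrected to say that the published mapping is void, without printing a new one.

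The cost is a one-off recoding of the presets and envelopes and a protocol correction. Sample size, treatment and assessments do not change. If the device took patient-specific codes, setting them up could take more work; the article does not give enough to cost that.

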### Ethics issues

The study protocol and consent forms have been approved by the Ethics Committee of the First Affiliated Hospital of Nanchang University (NO: Clinical medicine ethical review [2015] 043). Consent will be obtained from family members of all study participants.

### Baseline tests

Descriptive data will be collected before randomization. The descriptive data include gender, age, height, weight, nationality, education level, employment status, clinical syndrome (left-sided or right-sided brain injury), and the type, degree, and location of the TBI at diagnosis. Vital signs such as blood pressure, heart rate, respiratory rate, and body temperature will also be measured. The GCS and GOS, the tools used to assess the severity of DOC, will be applied at baseline to determine whether the two groups are consistent before the intervention.

### Intervention

The intervention group will receive conventional rehabilitation combined with active tDCS therapy, while the control group will receive conventional rehabilitation combined with sham tDCS therapy. The conventional rehabilitation consists of hyperbaric oxygen, cerebellar nuclear stimulation, limb electrical stimulation, and passive limb range-of-motion training. The treatments will be performed six times per week for 4 weeks. For quality management, all procedures performed by the therapists participating in this study will be standardized, including the study protocol, treatment methods, and assessments.

### Basic treatments

All participant will receive basic treatments following the *Guidelines for the Management of Severe Traumatic Brain Injury, Fourth Edition* [27]. Based on this guideline and the patient’s condition, the treating physician will manage each patient, including management of the use of drugs and prevention of complications.

### Hyperbaric oxygen

All participants will receive hyperbaric oxygen therapy. The hyperbaric oxygen chamber model is the *YC3200/0.3-22VII*. According to a similar study [28], the treatment parameters are as follows:

(1) treatment of pressure is 1.8~2.0 atmospheres absolute (ATA) ; (2) plus and minus pressure time is 25 min; (3) after adjusting the pressure via the voltage regulator, wearing a mask to absorb pure oxygen 30 min for twice and breathe in cabin air for 10 min during the interval of twice absorbing pure oxygen; or breathe pure oxygen 20 min for thrice and breathe in cabin air for 5 min during the interval of thrice absorbing pure oxygen.

### Cerebellar nuclear stimulation

All the participants will receive cerebellar nuclear stimulation. The model of the electro-bionic stimulator is the NK - IA05. A crescent electrode will be applied behind the ear to improve the posterior circulation in the brain. According to normal tolerance, the current intensity is about 15 mA, and the stimulus time is 30 min per treatment.

### Limb electrical stimulation

All the participants will receive limb electrical stimulation. This will be performed with 4 cm × 4 cm square electrodes, which will be attached to the extensor carpi radialis and the abdominal muscles of the tibialis anterior. The current intensity is according to use in sport, and the stimulus time is 30 min per treatment.

### Passive limb range-of-motion training

All the participants will receive passive limb range-of-motion training. The therapist will peform a total range of joint activities at the shoulder, elbow, hip, and knee. The training lasts 30 min per treatment.

### Active tDCS

The interventional group participants will receive active tDCS therapy. The anode of the electrode will be located in the dorsolateral prefrontal cortex (DLPFC) at the left side of the forehead, and the cathode will be located in the superior margin of the right orbit. The current intensity is 1–2 mA, and the square electrode has a range of 5 cm × 7 cm. The treatment parameters are as follows: (1) 20 min per treatment; (2) once per day; (3) six times per week.

### Sham tDCS

The control-group participants will receive sham tDCS therapy. The anode of the electrode will be located in the DLPFC at the left side of the forehead, and the cathode will be located in the superior margin of the right orbit. The current is only input in each 15 s of the initial stage, and there is no current output in the middle 19.5 min of the sham therapy. The remaining parameters are consistent with the active stimulus.

### Study endpoints

The study endpoints are as follows:
If serious adverse reactions occur during the test, the test will be terminated in time to protect the subjectsIn the case of serious complications or deterioration of the condition of the subject in the test, the test will be terminated if emergency measures are requiredIf the subject is required to withdraw from the clinical study, the test will be terminatedIf the patient is not cooperative and does not obey the treatment, and the treatment staff repeatedly explains that the treatment is ineffective, the test will be suspended

The investigator will record in detail the reason and time of a participants’s withdrawal from the study.

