### Outcome measures

In this study, primary outcomes will be measured at baseline and the end of every week from the 1st to the 4th week. Secondary outcomes will be measured at baseline and the end of the 4th week. During each treatment, adverse events and untoward effects will be assessed. After follow up (8 weeks), the prognosis and disability condition outcomes (GOS and Disability Rating Scale (DRS)) will also be evaluated. All outcome assessments will be independently performed by experienced and blinded assessors, the same one professional rehabilitation physician. A summary of all the measures in the trial is shown in Table 1.

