### Primary outcomes

#### Glasgow Outcome Scale

The GOS is used to assess the recovery and outcome of patients with TBI. The severity of disability is divided into 5 levels according to indicators such as whether the patients can recover to undertake work, study, and self-care. The 5 levels are death, vegetative state, severe disability, moderate disability and good recovery.

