### Safety assessments

The medical staff will record adverse events (AEs) that occur at any time during treatment. When a serious AE occurs, the Ethics Committee of the First Affiliated Hospital of Nanchang University will determine whether the participant needs to be withdrawn from the study. We will treat AEs free of charge.

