### Data collection and management

General baseline information will be collected about patients when they are sent to the hospital and will include the following: age, sex, nationality, education level, disease type, course of illness. Major indicators are assessed at the end of the 1st, 2nd, 3^rd^, and 4th week of treatment, including application of the GOS after 4 weeks of treatment, all secondary index evaluations: the BAEP, body feeling on USEP, and EEG data. For each treatment, safety is assessed in terms of adverse events and adverse reactions.

Outcomes will be assessed using the GOS at the end of 1st, 2nd, 3rd, and 4th week, and will be performed using the BAEP, USEP, and EEG at the end of the 4th week of treatment. Complications during follow up will also be assessed. If the patient is still in the hospital, the investigator may visit the patient on the ward to go through the evaluation. If the patient has been discharged, his or her legal representative will be told to come back in due time for assessment after leaving the hospital. If the patient does not arrive, the investigator will try to contact the patient or the family members by telephone. Other possible methods may also be used to explain the situation and complete the outcome assessment. If all attempts fail, no further contact will be made, and the patient will be recorded as lost to follow up.

All the data will be collected by independent investigators who are blind to the patient’s allocation. Each local study center will assign a specific investigator at the beginning of the trial. This investigator will be excluded throughout treatment of all the participants unless asked by clinicians to perform the assessment.

All variables specified in the protocol will be documented on standardized hard-copy case report forms (CRFs) in all participating centers. When the 8-week follow up is complete, data in the CRF of each patient will be validated for completeness, consistency, and plausibility, by an independent investigating physician in a local center. Then the CRF will be transmitted to the Center of Evidence Based Medicine, NCU, which will be responsible for the development of a central database, and data entry and storage. At the end of the trial, the database will be locked and sent to the study statistician for analysis based on a predetermined statistical analysis plan.

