### Statistics methods

#### Statistical analysis

SPSS21.0 software will be used to analyze the test results. In the descriptive analysis of the sample, continuous variables will be expressed by mean and standard deviation for normally distributed data, and median and interquartile range for non-normally distributed data. Normally distributed data variables will be statistically compared between groups using the *t* test. Ordinal-level variables with a non-normal distribution will be statistically compared between groups using the Mann–Whitney *U* test. Measures with a discrete distribution will be expressed as percentages and analyzed using the chi-squared (χ2) or Fisher’s exact test as appropriate. A general linear model or logistic regression model will be applied to adjust for confounding influences if necessary.

We will compare baseline characteristics between groups using the *t* test or Mann–Whitney test for continuous variables and the Pearson chi-squared or Fisher’s exact test for categorical variables. If statistical significance appears, the inequality factors will be treated as confounding variables in the final efficacy analysis. For comparison of the primary or secondary outcomes between groups, the *t* test or non-parametric tests will be used to analyze continuous data, and the Pearson chi-squared or Fisher exact test to analyze categorical data. To control for possible confounding variables, linear models or linear regression will be applied for dependent continuous variables and logistic regression models for dependent categorical variables. Subgroup analysis of the primary outcomes will be stratified by participants’ sex. Analysis of variance will be used for the repeated measurement data. Analysis of the primary and secondary outcomes will be on an intention-to-treat (ITT) and a per-protocol (PP) basis. The result of the ITT analysis will be compared with that of the PP analysis to determine whether the results are consistent. Missing data will be handled according to the method of last observation carried forward. Adverse events will be listed and analyzed using the chi-square test or Fisher’s exact test.

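### Stopping for a serious event combined with LOCF can replace a worse or fatal GOS with an earlier, better one, and can bias the primary comparison in either direction

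*Protocol article*

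**What the plan says.** All places are in the protocol article.

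- **Study endpoints.** The test is ended for serious adverse reactions, and in the case of "serious complications or deterioration of the condition of the subject in the test, the test will be terminated". The second rule has a condition that the quoted words do not reach: it applies only where emergency action is needed. The section closes by asking the investigator to record the reason for and time of a participant's "withdrawal from the study".
- **Safety assessments.** After a serious adverse event, the Ethics Committee "will determine whether the participant needs to be withdrawn from the study". Here withdrawal is decided case by case.
- **Outcome measures.** The "primary outcomes will be measured at baseline and the end of every week from the 1st to the 4th week". A further GOS is planned after the 8-week follow-up and is listed apart from the weekly primary ratings.
- **Glasgow Outcome Scale.** "The 5 levels are death, vegetative state, severe disability, moderate disability and good recovery".
- **Data collection and management.** Ward visits, recall of discharged patients and telephone contact are described, and then: "Other possible methods may also be used to explain the situation and complete the outcome assessment". The section does not say whether this covers patients who were stopped.
- **Statistical analysis.** "Analysis of the primary and secondary outcomes will be on an intention-to-treat (ITT) and a per-protocol (PP) basis". "Missing data will be handled according to the method of last observation carried forward". No other missing-data method is given. Adverse events are compared between arms separately.

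**The concern.** LOCF assumes that a patient's level would have stayed where it was last seen. The stopping rules select patients for whom that assumption is least plausible: those with a serious reaction, or a complication or deterioration grave enough to need emergency action. If their GOS is not rated afterwards, the value analysed at week 4 usually predates the reason for its absence. For example, if a patient is stopped in week 2, is not rated again and dies in week 3, and the death is not entered as a GOS, the patient is analysed at the week-1 level. Yet the scale has a level for exactly this outcome.

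At stake is the primary efficacy estimate. If such events differ in frequency between the arms, LOCF removes part of a real difference, and the reader cannot tell how much. The per-protocol comparison does not help, because it does not recover the outcomes after stopping either. The separate adverse-event comparison may show an excess of harm, but it does not correct the GOS estimate.

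**Working it through.** **Inputs from the article.** The plan's own figures here are the arm size and the dropout allowance (Sample size section). With the larger SD of 2.51 and a difference of 2.01 GCS points, n = 2 × (1.960 + 1.282)² × 2.51² / 2.01² = 32.8, so 33 per group, as stated. Then 33 × 1.2 = 39.6, so 40 per group, as stated. The 20% allowance is 0.20 × 40 = 8 patients per arm, from all causes. The article gives no rate of stopping, deterioration or death, so every rate below is an assumption.

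**Size per hidden event.** Code GOS from 1 (death) to 5. An unrecorded death carried forward at level 2 adds (2 − 1)/40 = 0.025 to the arm mean. Carried forward at level 3, it adds (3 − 1)/40 = 0.05.

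**General form.** Let p be the proportion of an arm whose worsening is hidden, and L the mean number of levels hidden per such patient. Then

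bias in (active − sham) = p_active × L_active − p_sham × L_sham.

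A positive value flatters active tDCS and a negative value flatters sham. If the rates and the last observed levels are the same in both arms, the bias is zero, although both arms look better than they are.

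**Illustration 1: one-level falls.** Assume 40 per arm, 25% of the other patients gain one level in both arms, and each deteriorating patient falls one level unseen. An arm's mean change is 0.25(1 − p) − p in truth and 0.25(1 − p) under LOCF. The differences are therefore −1.25(p_active − p_sham) and −0.25(p_active − p_sham). In this setting LOCF removes 1/1.25 = 80% of the true difference. The detection rates come from 4,000 simulated trials with baseline GOS 2 or 3 equally likely. They count a two-sided 5% Mann–Whitney result against active.

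| Deterioration, active / sham | True difference | LOCF difference | Harm detected, true GOS | Harm detected, LOCF |
|---|---|---|---|---|
| 20% / 20% | 0 | 0 | 2% | 2% |
| 20% / 10% | −0.125 | −0.025 | 10% | 4% |
| 30% / 10% | −0.250 | −0.050 | 27% | 5% |
| 40% / 10% | −0.375 | −0.075 | 53% | 6% |

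**Illustration 2: the reverse imbalance.** Suppose 4 of 40 active and 8 of 40 sham patients fall one level unseen, with nothing else differing. The true difference is (8 − 4)/40 = +0.10 and LOCF shows 0. Here a benefit is hidden.

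**Illustration 3: an extreme case.** Baseline is 2 or 3 equally likely, so a death costs 1.5 levels on average. Assume unrecorded deaths in 20% of active and 5% of sham patients, and one-level gains in 40% and 10% of the rest.

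- LOCF: 0.40 × 0.80 − 0.10 × 0.95 = 0.320 − 0.095 = +0.225.
- Truth: (0.320 − 0.20 × 1.5) − (0.095 − 0.05 × 1.5) = 0.020 − 0.020 = 0.

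In simulation the test favoured active in 29% of trials under LOCF, against 4% with the true outcomes. This shows what the rule can do, not what to expect.

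**The case against.** The strongest reply is that the article does not say that assessment ends at a stop. Ending the test may mean ending stimulation, assessment or both. The Data collection and management section provides for ward visits and other attempts to complete ratings, and does not exclude stopped patients. A known death can be scored, so it need not be missing at all. Details of follow-up after a stop may also sit in the full protocol or in the analysis plan that the article mentions.

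Much of this stands, and it rules out several stronger readings that a reader might infer:

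- *Every patient who deteriorates leaves the study.* Not supported. The deterioration rule has the emergency condition, and the Safety assessments section leaves withdrawal after a serious adverse event to the Ethics Committee.
- *No GOS is planned after a stop.* Not stated. The text is unclear rather than prohibitive.
- *Uncooperative patients are removed and frozen at an earlier level.* The text has the test suspended for them. That refusal may signal returning awareness is speculation.
- *The analysis is not intention-to-treat.* Imputation keeps all randomized patients. The problem is the quality of the imputed values.
- *The primary analysis hides harm.* This needs worsening after the last rating, no record of it as a GOS, and more of it on active. Gradual worsening may already show in earlier weekly ratings, and the adverse-event comparison gives a second view of harm.

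The extreme illustration is also rightly criticised. It uses the whole allowance of 8 active patients as unrecorded deaths, in a population that must be stable at entry.

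The reply does not remove the point. LOCF is a stated rule, not a detail left for later, and it is the only one. The stops are tied to worsening, and the section that lists them calls the result withdrawal. The emergency condition reduces the number of patients affected but strengthens the link with outcome.

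**Conclusion.** The concern holds in a conditional form. Where the GOS after a stop is missing, the missingness depends on the outcome, and LOCF can substitute an earlier, better level for a worse or fatal one. The between-arm bias may favour either arm. It can hide harm if events are commoner on active tDCS, hide benefit if commoner on sham, and is about zero if event rates and gains are equal.

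The size cannot be determined from the article. The firm figure is 0.025 to 0.05 level of an arm mean per hidden death, for a last GOS of 2 or 3 and 40 per arm. The 80% loss of a true difference and the +0.225 spurious gain hold only under the assumed rates. The Study endpoints and Safety assessments sections also differ on what follows a serious event and must be reconciled. This should be fixed: the rule can give a wrong answer on the primary outcome, but neither the direction nor the frequency is established.

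**What to change.** Leave the clinical stopping criteria unchanged.

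1. **Study endpoints and Safety assessments:** reconcile the two sections. State that stopping stimulation does not end outcome assessment unless consent is withdrawn.
2. **Data collection and management:** state that the weekly and 8-week GOS continue for stopped patients, with the existing blinded assessor and the contact procedures already described.
3. **Statistical analysis:** use these observed ratings in the intention-to-treat analysis, and score any death before a visit at the GOS death level.
4. **Statistical analysis:** replace LOCF as the primary method for the weekly GOS with a model-based one, for example an ordinal mixed model or multiple imputation using the weekly GOS and the reason for stopping. These methods also rest on assumptions about unseen values, so continued rating is the main repair.
5. **Sensitivity analysis:** place patients who were stopped for a serious event and not rated later at the worst level.

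The cost is some rewording and a few more ratings, and the efficacy estimate may become less favourable. Ratings not taken during the trial may not be recoverable later, so items 1 and 2 belong before enrolment. Items 3 to 5 need only be settled before unblinding.
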